### Training sessions

First, all patients will undergo preoperative assessment and rehabilitation education, including investigation of the patient’s basic information, medical history, and therapeutic schedule, and they will be taught how to undergo rehabilitation. Patients will be taught according to the special BC Rehabilitation Mission Manual to strengthen their understanding regarding the importance of postoperative rehabilitation of BC and to increase their compliance.

The exercise program will be divided into four phases. Phase 1 will consist of the following four movements: (1) The isometric handgrip exercise will be adapted for 2 min of 5-s contraction and 5-s rest-pause intermittently per set, 3 sets per day. (2) The isotonic contraction exercises of the wrist and elbow will not be loaded. Full range of joint motion will be performed, 10–15 times per set in each direction, 3 sets per day. (3) Isometric contraction of the shoulder joint will be performed in both the flexion and abduction directions. Muscles will be allowed to contract for 10 s and rest for 5 s, 10–15 times per set in each direction, 3 sets per day.

Phase 2 will be the isotonic contraction of the shoulder joint in both flexion and abduction. According to the pre-training assessment results, researchers will adjust the appropriate ROM for patients with gravity as the load, 10–15 times per set in each direction, 3 sets per day.

Phase 3 will involve active stretching of the shoulder flexion and abduction. The patient will be asked to face or side face the wall, place her hand on the wall, and slowly crawl her fingers upward. When the patient feels that the armpit has a slight pulling or pain, she will be asked to stop moving her fingers, stretch the shoulder joint for 20–30 s, and then slowly move the arm away from the wall. The same movement will be repeated 10–15 times per set, 3 sets per day.

Phase 4 will involve PRT of shoulder flexion and abduction. Based on the ROM and muscle strength results of the pre-training assessment, the researchers will adjust the appropriate resistance to allow the patients to lift repetitively for 8–15 times per set, 3 sets per day. Providing resistance can be achieved through equipment, such as elastic bands and barbells.

All subjects need to perform the routine exercises of phases 1 and 3, regardless of group assignment. According to the different group assignments, the patients will perform the exercises of phases 2 and 4 at different times. Relevant concomitant care is permitted for all patients.

### Training timelines

The patients will be divided into four groups: A, B, C, and D. All patients will start the rehabilitation training of phases 1 and 3 separately on the first day and the second week after surgery. The training timings of phases 2 and 4 are slightly different in different groups. Group A will start phase 2 at 1 week after surgery and phase 4 at the fourth week after surgery. Group B will also start phase 2 at 1 week after surgery, but they will start phase 4 in the third week after surgery. Group C will advance the start of phase 2 to the third day after surgery, but they will not start phase 4 until the fourth week after surgery. Group D will not only advance the start of phase 2 to the third day after surgery, but they will also initiate phase 4 to the third week after surgery, 1 week ahead of schedule.

During the trial, patients will stay in the hospital or return to the hospital regularly for chemotherapy, to ensure that they can be directly instructed. After patients are fully discharged, the training meeting will be instructed and completed in the form of a home exercise, program lasting for 6 weeks, 3–5 sets per week. A video of each patient’s exercise session should be sent to the therapist for examination.

### Outcomes

#### Primary parameter

CMS is a method that records individual parameters and provides an overall clinical functional assessment of the shoulder, and it is sufficiently sensitive to reveal even small changes in shoulder function [27, 28]. The score consists of the following four domains: pain (1 item), activities of daily living (ADL; 3 items for activity level, i.e., work, sports, sleep; 1 item for hand positioning, i.e., rotation), mobility (4 items: forward and lateral abduction/elevation, external and internal rotation), and strength (1 item) [29]. Pain and the three items for the activity level of ADL will be obtained from the patient, which means that patients will be self-assessed, while all other items will be assessed by the physiotherapist. The method of assessment will consist of clinical examination plus patient interview. The complete assessment only requires 5–7 min to perform [30]. All items are easy to understand and not emotionally sensitive. The respondent burden is minimal. The assessment of retest reliability using the intraclass correlation coefficient is 0.80–0.96, which indicates that the items in each scale are highly correlated with one another compared with items of another scale [31].

#### Secondary parameters

Quality of life (QOL) is a multidimensional, subjective construct that reflects physical, mental, and social health domains of patients [32]. The European Organization Research and Treatment of Cancer (EORTC) QLQ-BR23 questionnaire is one of the most available tools for assessing aspects of QOL for BC patients [33]. It contains 23 items divided into two functional scales, including body image and sexuality, and three symptom scales, including arm symptoms, breast symptoms, and systemic therapy side effects. This questionnaire has been found to have a high internal consistency for 4 out of 5 scales and well-known group discriminative ability [34]. The validity of the EORTC QLQ-BR23 has been internationally scrutinized and explored in many countries, which has ultimately confirmed the questionnaire’s validity in BC [35].

The SF-36 is a general brief self-report questionnaire that assesses health-related QOL. The SF-36 contains 36 items that measure eight multi-item variables, including physical functioning, social functioning, role limitations due to physical problems, role limitations due to emotional problems, mental health, energy and vitality, bodily pain, and general perception of health, and there is a single-item scale on health transition. The score of each item ranges from 0 to 100. For each variable, the item scores are calculated, and a higher score indicates a better health status [36]. The internal consistency of the variables in the SF-36 is assessed with Cronbach’s α statistic and test-retest reliability [37]. Studies have shown that the SF-36 is acceptable for patients, and it has a high level of internal validity and good test-retest properties [38].

The assessments of shoulder function and quality of life will be evaluated at 1 week, 3 weeks, and 9 weeks after surgery.

In addition, joint mobility, muscle strength, grip, circumference, PDV, and pain, the parameters of exercise intensity in the pre-assessment, will also be evaluated as outcomes. Assessment methods and principles are the same as those for pre-assessments.

Shoulder ROM and strength will be assessed at postoperative 3 days and 1, 2, 3, 6, and 9 weeks. Grip will be evaluated at postoperative 1 day, 3 days, and 1, 2, 3, and 6 weeks, and upper limb circumference will be assessed at postoperative 1 day and 3, 12, and 18 weeks. PDV, pain, and skin will be evaluated by interview and palpation at postoperative 1 day, 3 days, 1 week, and 2 weeks.

CMS, EORTC QLQ-BR23, and SF-36 will be required to be completed during the follow-up sessions at 12 and 18 weeks after surgery. During the follow-up sessions, information related to clinical testing, laboratory testing, and adverse events will be collected and assessed. Patients will be followed up in the ward during chemotherapy, and it is supplemented by telephone or WeChat.

Figure 2 shows a diagram of the study design.

**Fig. 2 Fig2:**
[figure not shown]
The study design

### Data analysis

#### Sample size

By estimating the sample size of the k-group sample mean comparison in a completely random design, the improvement scores for the CMS of the four groups of patients at 84 days after treatment were 15, 16, 18, and 19, and the standard deviations were 2, 2.5, 2.5, and 3, respectively. The assumption was that *α* = 0.05 and 1-*β* = 0.9. After calculation using PASS software (11.0), a total of 164 patients were required to be treated, and a 20% loss rate was calculated. Each group required 50 patients [39].

The calculation formula was as follows:
$$ n=\frac{\psi^2\left[{\sum}_{i=1}^k\frac{S_i^2}{k}\right]}{\left[{\sum}_{i=1}^k\frac{{\left(\overline{X_i}-\overline{X}\right)}^2}{\left(k-1\right)}\right]}. $$

### Statistical analyses

Analyses will be performed using SPSS statistical software (version 20.0) by a statistician in the Department of Rehabilitation Medicine, Zhongnan Hospital of Wuhan University. Data will be analyzed according to the “intention-to-treat” (ITT) principle. A two-sided significance level of 5% will be used for all analyses. If the experimental data satisfies the normal distribution and the homogeneity of the variance, one-way analysis of variance (ANOVA) will be performed for comparison among the 4 groups with respect to the CMS, EORTC QLQ-BR23, SF-36, ROM, strength, grip, circumference, PDV, and pain. If there is an overall difference, the Tukey method for multiple comparisons will be used to compare the differences between groups at each time point. The results of repeated measurement ANOVA testing at each time point in each group will be analyzed by repeated measures to observe the recovery of patients at different times after surgery. For data with irregular variance, variable transformation can be used after the Kruskal-Wallis *H* test.

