**Design:**

This is a randomized controlled trial. Female participants with BC who are scheduled to undergo mastectomy, including unilateral total breast or breast-conserving surgery plus axillary lymph node dissection, will be enrolled in this study. The intervention includes the following: 200 participants will be allocated using a 1:1:1:1 ratio to the A, B, C, and D groups, which have four different rehabilitation timelines for four phases of rehabilitation exercises. A therapist will evaluate the patient’s overall health and then adjust the training intensity before initiating training. The assessments include upper limb mobility, grip, limb circumference, postoperative drainage volume (PDV), and pain. The training will last for 12 weeks, and patients will undergo follow-up twice within 6 weeks after discharge. Outcomes include the following: Constant-Murley Score (CMS) is the primary parameter. European Organization Research and Treatment of Cancer Quality of Life Questionnaire-BR23 (EORTC QLQ-BR23), SF-36, range of motion (ROM), strength, grip, circumference, PDV, and pain are the secondary parameters. All enrolled subjects will be assessed at 1 day, 3 days, 1 week, and 2, 3, 6, 9, 12, and 18 weeks after the surgery.

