**Discussion:**

This is a randomized controlled trial to evaluate the effect of different rehabilitation training timelines to prevent shoulder dysfunction among postoperative patients with BC. If the results are confirmed, this study will establish an optimal timeline for postoperative BC rehabilitation.

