### Aim of this study

The aims of this study are as follows:
Observation of the optimal active exercises of the shoulder joint under full evaluation at 3 days after surgery, with respect to whether it accelerates the recovery of shoulder function and improves the quality of life of postoperative patients with BC. Evaluation of whether early-stage rehabilitation training leads to an increase in PDV, which affects shoulder function and the time of extubation in BC patients.Observation of progressive resistance training (PRT) in the case of full evaluation at 3 weeks after surgery, with respect to whether it promotes the recovery of shoulder function.

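### A flat 5% level covers eight secondary outcomes at each of their own visits, with no error control across outcomes or visits, so isolated secondary findings cannot carry a confirmatory claim

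*Protocol article*

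**What the plan says.** The Abstract (Design) sets a single primary outcome: "Constant-Murley Score (CMS) is the primary parameter". It lists eight secondary outcomes, beginning with the EORTC QLQ-BR23 and continuing "SF-36, range of motion (ROM), strength, grip, circumference, PDV, and pain are the secondary parameters".

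Statistical analyses fixes one level for everything: "A two-sided significance level of 5% will be used for all analyses". It specifies a one-way ANOVA across the four groups for the primary and all eight secondary outcomes. If the overall test shows a difference, "the Tukey method for multiple comparisons will be used to compare the differences between groups at each time point". No error control, ordering or exploratory status across outcomes or visits is stated.

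Secondary parameters describes both quality-of-life instruments by scale. Of the QLQ-BR23 it says "It contains 23 items divided into two functional scales, including body image and sexuality, and three symptom scales"; of the other instrument, "The SF-36 contains 36 items that measure eight multi-item variables". No total score is mentioned for either.

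Aim of this study asks, in its first aim, whether early active exercise "accelerates the recovery of shoulder function and improves the quality of life of postoperative patients with BC". Its second aim asks whether early training increases postoperative drainage volume (PDV). Quality of life and PDV are measured only by secondary outcomes.

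**The concern.** Tukey's method handles the six pairwise comparisons among four groups within one ANOVA. It does nothing about repeating that ANOVA over eight outcomes and several visits, each at 5%. With four arms, chance findings on different scales or visits can also favour different timelines, and the text does not say which secondary result would answer the quality-of-life question.

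Four of the tests have a further problem. Grip, circumference, PDV and pain are measured on day 1. Under Training timelines, all groups start phase 1 on day 1, and the arms first diverge when groups C and D start phase 2 on day 3. A between-group difference on day 1 cannot be an effect of the timelines.

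At stake is how the secondary results are read. A single significant scale at a single visit could be reported as evidence for one timeline when it is what chance would be expected to produce.

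**Working it through.** The article states no familywise error rate, so there is no figure of its own to reproduce. The check counts the tests and then computes the chance of at least one false positive when the four timelines are equivalent.

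**Count** (visits from Secondary parameters and the follow-up paragraph after it)

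| Outcome | Visits | Tests |
|---|---|---|
| QLQ-BR23 | weeks 1, 3, 9, 12, 18 | 5 |
| SF-36 | weeks 1, 3, 9, 12, 18 | 5 |
| ROM | day 3; weeks 1, 2, 3, 6, 9 | 6 |
| Strength | day 3; weeks 1, 2, 3, 6, 9 | 6 |
| Grip | days 1, 3; weeks 1, 2, 3, 6 | 6 |
| Circumference | day 1; weeks 3, 12, 18 | 4 |
| PDV | days 1, 3; weeks 1, 2 | 4 |
| Pain | days 1, 3; weeks 1, 2 | 4 |

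Total: 5 + 5 + 6 + 6 + 6 + 4 + 4 + 4 = 40, taking one score per outcome and one overall test per visit. Testing the scales separately gives (5 + 8) × 5 = 65 quality-of-life tests alone.

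**Independent tests.** The chance of at least one false positive among m tests is 1 − 0.95^m.
- m = 40: 1 − 0.95^40 = 87.1%, with 40 × 0.05 = 2 false positives expected.
- m = 8 (each outcome at one time point): 1 − 0.95^8 = 33.7%.
- m = 65: 1 − 0.95^65 = 96.4%.
- m = 4 (day 1 only): 1 − 0.95^4 = 18.5%.

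**Correlated tests.** Outcomes and visits in the same patients are correlated, which lowers these rates. The article gives no correlations, so they are assumed over a range. Simulation: four groups of 40 (50 per group less the planned 20% loss), normal data, no true differences, one common correlation, F test at 5%, 10,000 replicates.

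| Tests | ρ = 0 | 0.3 | 0.5 | 0.8 |
|---|---|---|---|---|
| 40 | 87% | 74% | 59% | 31% |
| 8 | 34% | 30% | 26% | 17% |
| 65 | 97% | 86% | 69% | 35% |
| 4 (day 1) | 19% | 17% | 16% | 12% |

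Smaller runs of the same design gave 30% for 40 tests and 16% for 8 tests at ρ = 0.8. The ranges are therefore quoted as about 30% to 87% and about 16% to 34%.

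**Separate correlations.** A second simulation (41 per group, 3,000 replicates per setting) used a between-outcome correlation of 0 to 0.7 and a between-visit correlation of 0.3 to 0.9. The 40-test rate ran from 36% to 85% and exceeded 50% in 14 of 16 settings. For the 28 quality-of-life, ROM, strength and grip tests it ran from 30% to 74%, above 50% in 10 of 16. For the 10 quality-of-life tests on total scores it ran from 17% to 37%.

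**The case against.** The strongest reply is that ordering secondary outcomes, or calling them exploratory, is commonly left to the statistical analysis plan, which is not shown. The outcomes are already labelled secondary beneath one named primary, and the sample size rests on the primary score alone. This stands in part: a missing hierarchy would not be a finding by itself. But the article does state a rule, one level for all analyses with comparisons at each time point. A later plan that reserved the 5% claim for a few tests would have to depart from that sentence.

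A second reply is that the time-point wording is attached to the Tukey step, so 40 overall tests are not explicitly prescribed. That is fair, and 40 is a reading. One overall test per outcome at a single time point still gives about 16% to 34%.

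Third, a day 1 difference would be read as baseline imbalance, not as benefit. Probably so, which is a reason not to test it.

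Some stronger readings are tempting, and the documents do not support them:
- *A false quality-of-life or function claim is more likely than not.* This depends on the assumed correlations and on how scales are counted. For quality of life on total scores, the rate stays below 50% even under independence (1 − 0.95^10 = 40.1%).
- *Every outcome is tested at every visit with no adjustment.* Each outcome has its own 4 to 6 visits, and Tukey is specified within each ANOVA.
- *All the aims rest on secondary outcomes.* Shoulder function is covered by the primary score; only quality of life and PDV depend on secondaries.
- *The trial promises a quality-of-life benefit.* The aim is phrased as a question, and the abstract's statement, "If the results are confirmed, this study will establish an optimal timeline for postoperative BC rehabilitation", is conditional and names no secondary outcome.

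**Conclusion.** The point holds as a limit on what the secondary results can support. The stated rule gives no familywise control across outcomes or visits. If the timelines are equivalent, the chance of at least one false-positive secondary result is about 30% to 87% over 40 tests, and about 16% to 34% for eight outcomes at one time point. Even the lowest figure is about three times the stated 5%.

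These rates rest on no true difference in any outcome, normal data, common correlations from 0 to 0.8 that the article does not supply, one score per outcome, and a reading of the time-point wording that includes the overall tests. Separate testing of the quality-of-life scales would raise them. The primary Constant-Murley conclusion is not touched by this point.

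**What to change.** Amend Statistical analyses as follows.

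1. Reserve the 5% significance claim for the primary Constant-Murley comparison. If the sponsor wants a confirmatory quality-of-life claim, name one scale and one time point of its own choosing, tested only if the primary is significant.
2. Label all other secondary outcomes, scales and visits exploratory, and report them as group differences with 95% CIs.
3. Report PDV, circumference and pain as estimates with 95% CIs outside any gate, so that a non-significant primary result does not suppress a harm signal.
4. Drop the between-group tests of grip, circumference, PDV and pain on day 1, before the arms differ.

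This costs a few sentences, with no new data and no more patients. The downside is that fewer secondary results can be called significant.

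### Drainage volume, grip, pain and arm circumference each have a day 1 reading taken before the groups' programmes differ, but the stated four-group test of later readings does not use it and so loses precision

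*Protocol article*

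**What the plan says.** All references are to the protocol article.

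- **Between-group test (Statistical analyses).** If normality and equal variance hold, "one-way analysis of variance (ANOVA) will be performed for comparison among the 4 groups with respect to the CMS, EORTC QLQ-BR23, SF-36, ROM, strength, grip", and also circumference, PDV and pain. After an overall difference, "the Tukey method for multiple comparisons will be used to compare the differences between groups at each time point". No covariate is named. For data that fail the assumptions, the section offers the Kruskal-Wallis test and transformation, also without a covariate.
- **Repeated measures (Statistical analyses).** "The results of repeated measurement ANOVA testing at each time point in each group will be analyzed by repeated measures". The stated purpose is to follow recovery over time, so this is a within-group description.
- **Level (Statistical analyses).** "A two-sided significance level of 5% will be used for all analyses".
- **Day 1 readings (Secondary parameters).** "PDV, pain, and skin will be evaluated by interview and palpation at postoperative 1 day, 3 days, 1 week, and 2 weeks". "Grip will be evaluated at postoperative 1 day, 3 days, and 1, 2, 3, and 6 weeks". Circumference is read on day 1 and at weeks 3, 12 and 18.
- **When the groups diverge (Training timelines).** All four groups start phase 1 on day 1. The first difference is on day 3: "Group C will advance the start of phase 2 to the third day after surgery", and group D does the same, while A and B wait until 1 week.
- **Second aim (Aim of this study).** "Evaluation of whether early-stage rehabilitation training leads to an increase in PDV, which affects shoulder function and the time of extubation in BC patients".

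**The concern.** A day 1 reading taken while all groups follow the same programme can serve as a baseline, whether or not allocation was already known by then. Later drainage is likely to depend partly on the operation, and eligibility covers both total mastectomy and breast-conserving surgery. Later grip is likely to depend partly on the woman's own strength. An unadjusted ANOVA leaves that predictable part in the error term. At day 1 itself the plan's wording provides for a between-group test in which any difference can only be chance.

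PDV is where this counts most. Whether early training raises drainage is a harm question, and the sample size was set for the CMS alone. The less precise the PDV comparison, the more easily a real increase goes undetected. The estimated difference also carries whatever day 1 imbalance happened to arise.

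**Working it through.** **1. Is there a figure in the plan to reproduce?** Not for these outcomes: the article gives no SD, effect size, power or correlation for PDV, grip, pain or circumference. Its only power figure is 90% for the CMS, with 164 women before loss. I could not reproduce 164. The mean variance is (4 + 6.25 + 6.25 + 9)/4 = 6.375, and the four means have mean squared deviation 10/4 = 2.5. Noncentral F then needs 11 per group, or 44 in total. That is a separate matter and does not enter below.

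**2. Which outcomes have a usable baseline?**

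| Outcome | First outcome reading | Before groups diverge on day 3? |
|---|---|---|
| PDV, pain | day 1 | yes |
| Grip | day 1 | yes |
| Circumference | day 1 | yes |
| ROM, strength | day 3 | not clear |
| CMS, QLQ-BR23, SF-36 | week 1 | no |

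The point covers the first three rows only.

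**3. Variance.** With correlation ρ between the day 1 and later readings, analysis of covariance leaves a residual variance of (1 − ρ²) times the unadjusted one:

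- ρ = 0.3: 1 − 0.09 = 0.91, a fall of 9%
- ρ = 0.5: 1 − 0.25 = 0.75, a fall of 25%
- ρ = 0.7: 1 − 0.49 = 0.51, a fall of 49%

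Change from day 1 would not do the same job. With equal variances its variance is 2(1 − ρ) times the raw one, which at ρ = 0.5 is exactly 1, so nothing is gained.

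**4. Power.** Inputs: 4 groups, two-sided α = 0.05 (Statistical analyses), and 200 women less 20% = 160, or 40 per group. Two inputs are assumptions: ρ and the unadjusted power.

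- Find the noncentrality λ that gives the chosen unadjusted power on F(3, 156).
- Replace λ by λ/(1 − ρ²) and use F(3, 155), since the covariate costs one error degree of freedom.

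Example: 70% unadjusted power needs λ = 9.015. At ρ = 0.5, λ becomes 9.015/0.75 = 12.02 and power becomes 83.1%, a gain of 13.1 points.

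| Unadjusted power | Gain, ρ = 0.3 | Gain, ρ = 0.5 | Gain, ρ = 0.7 |
|---|---|---|---|
| 30% | 2.7 | 9.2 | 25.3 |
| 40% | 3.6 | 11.8 | 30.2 |
| 50% | 4.2 | 13.4 | 31.5 |
| 60% | 4.6 | 13.9 | 29.7 |
| 70% | 4.5 | 13.1 | 25.1 |
| 80% | 4.0 | 10.8 | 18.2 |
| 90% | 2.7 | 6.7 | 9.7 |

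With 41 or 50 per group the gains agree to within 0.1 point, because the effect is solved to match the unadjusted power. A two-group contrast at ρ = 0.5 gives similar gains: 10.4, 12.4, 9.9 and 6.3 points from 40%, 60%, 80% and 90%.

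**5. Limits of the calculation.** It assumes normal errors and an effect that is present at the reading tested. The article does not say whether the day 3 reading comes before or after the first phase 2 session in C and D, so the figures apply most clearly from week 1 on.

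**The case against.** The strongest reply is that this is a preference for efficiency. After randomization an unadjusted ANOVA holds its type I error, and chance imbalance at day 1 is part of what the 5% level already allows for. The outcomes are secondary, grip appears in none of the aims, and covariates are often settled in an analysis plan that is not shown. The point about validity stands: a reader might infer bias or an invalid test, and neither follows. The point about the analysis plan does not stand, because the article itself names the between-group test for these outcomes.

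Other replies also hold in part.

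- **PDV may not be analysed by ANOVA at all**, given the normality condition. True, but the fallback is unadjusted too.
- **Drains come out at different times.** Later PDV may then be zero or absent, a plain log transform fails, and day 1 volume may predict such readings poorly. This stands and limits the gain at week 2.
- **Day 1 readings have other uses.** They enter the within-group repeated-measures analysis and help to set exercise intensity. That is correct, but neither use adjusts the group comparison.
- **A non-significant PDV result does not show absence of harm.** Analysis of covariance does not cure that; it only narrows the uncertainty.

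A reader might also infer that PDV is the only measured outcome behind the second aim. It is not: that aim names shoulder function, which the CMS measures. Of the three things named there, only time of extubation is missing from the listed outcomes.

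**Conclusion.** The point holds as a loss of precision on four secondary outcomes, of which PDV matters most. The plan collects a baseline common to all groups and does not use it in the test that compares them.

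The size rests on two assumptions that the article cannot settle. At ρ = 0.3 the gain is at most about 5 power points. At ρ = 0.5 it is about 11 to 14 points if unadjusted power is 40% to 80%, and about 7 points at 90%. A general loss of more than 10 points might be inferred from the middle of the table, but the article supports no such unconditional figure.

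The primary outcome is untouched. The CMS, like QLQ-BR23 and SF-36, is first read at week 1, after C and D have started phase 2, so that reading is not a baseline and should not be used as one. The change is worth making because it bears on a stated harm question and costs almost nothing.

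**What to change.** In Statistical analyses, replace the unadjusted comparison of PDV, grip, pain and circumference as follows.

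1. At each reading after day 1, fit an analysis of covariance with group and the woman's own day 1 value of the same measure. Report Tukey-adjusted differences of the adjusted means.
2. Drop the between-group test at day 1 and describe those values by group instead.
3. For PDV, use a method that tolerates zeros, such as log(x + 1) or a rank-based analysis of covariance. State in advance how removed drains are handled: either count readings after removal as zero, or limit the analysis to readings when drains are still in place. If the second is chosen, define it by scheduled time point, not by picking the women who still have a drain, because the second aim itself treats time of extubation as something that training may affect.
4. Leave CMS, QLQ-BR23 and SF-36 outside this change.

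The cost is a few sentences and one error degree of freedom. The readings are already scheduled. Expect little gain for PDV at week 2 if many drains are out by then.
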